### Participant Recruitment and Eligibility Criteria

Women recently diagnosed with breast cancer starting (neo-)adjuvant chemotherapy (a combination of taxanes and anthracyclines or only one of the treatments or in combination with radiation therapy or endocrine therapy) are recruited from Haukeland University Hospital. Patients in the usual care group (see above) will also be recruited from Uppsala University Hospital. All potential participants must fulfill the following eligibility criteria: (1) diagnosed with stage I-III breast cancer, (2) >18 years old, (3) can understand and communicate in the Norwegian or Swedish language, and (4) scheduled to undergo (neo-)adjuvant chemotherapy with a combination of taxanes and anthracyclines or only one of the treatments or in combination with radiation therapy or endocrines. Women who are (1) not able to perform basic activities of daily living, (2) show cognitive disorders or severe emotional instability, and (3) experiencing other disabling comorbidities that might hamper physical training (eg, heart failure, chronic obstructive pulmonary disease, orthopedic conditions, neurological disorders) will be excluded. All eligible women will receive written information. Women who meet the inclusion criteria will be offered further information and invited to query any question about the study before being invited to participate.

### Sample Size

Power calculations are based on findings in the Physical Exercise and Prostate Cancer trial [32], but findings from the study by Mijwel et al [12] strongly support similar expectations on chemotherapy in patients with breast cancer. With a similar effect on muscle fiber CSA, we need 10 participants in each group to obtain a statistical power of 80% in this study; to further enhance the power up to 95%, we need 16 participants. To account for dropouts during the intervention, we aim to recruit 40 participants to the training groups (20 in each group) willing to undergo muscle biopsies. We expect approximately 50% of the recruited participants will be willing to undergo muscle biopsy; therefore, we aim to recruit 80 participants to the training groups. To increase power on other measurements, the participants unwilling to undergo biopsy will be included in this study. In the usual care group, we also aim to include 20 participants willing to undergo muscle biopsies. This group will consist of patients living too far away from the study site at Haukeland University Hospital and participants in the usual care control group recruited to another substudy within the Phys-Can consortium carried out at Uppsala University Hospital [31].

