Endurance training has been reported to reduce the cardiotoxic effects of anthracyclines in rodents [21-23]. The possible protective effects of physical training on skeletal muscles during chemotherapy for breast cancer have only been studied in 1 small-scale study. Mijwel and colleagues [12] showed that participating in a training program that combined high-intensity intervals to either strength training or aerobic exercise (moderate intensity) during treatment had beneficial effects on muscle fiber CSA and mitochondrial enzymes in the 2 intervention groups. Furthermore, these beneficial effects showed an inverse correlation with changes in cancer-related fatigue, indicating that the training effect on muscle fiber CSA and mitochondrial enzymes during chemotherapy might reduce cancer-related fatigue [12]. However, there is a need for studies including more participants to verify these findings and to investigate the physiological mechanisms underlying this protective effect. Regular exercise during treatment also seems to have several other beneficial effects on both treatment efficiency and reducing the other side effects of treatment [24,25]. Some of these effects seems to be related to increased production of antitumor myokines in the exercising muscles [26], and this aspect will also be investigated in the analyses of muscle biopsies in this study.

To date, most studies have compared a single exercise intervention to usual care or interventions with no physical activity. High-intensity training is shown to induce larger improvements in VO_2max_ and muscle strength in both healthy individuals and in various patient populations [27-29]. However, it is not known to which extent chemotherapy interferes with normal adaptation to physical training. A recent systematic review and meta-analysis reported that longer sessions and higher weekly volume and duration are associated with more beneficial changes in VO_2max_ after endurance training in various populations with cancer during (neo)adjuvant treatment [30]. However, the effects of different training intensities were unclear.

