Data from the main study under the Physical Training in Cancer (Phys-Can) consortium showed that combined strength and endurance training with both low-to-moderate intensity and high intensity was feasible in patients with different types of cancer. Furthermore, high-intensity training led to better effects on muscle strength and VO_2max_ compared to low-to-moderate intensity training [29]. However, muscle biopsies were not included in the main study; therefore, how training with different intensities affect muscular cellular outcomes is not known. Thus, there is a need for more studies examining the effect of high versus low-to-moderate intensity training during treatment and especially those including muscle biopsies.

In summary, the direct effects of chemotherapy on muscle tissue in women treated for breast cancer are mostly unknown and previous studies that have investigated the direct effects of (neo-)adjuvant chemotherapy on muscle tissue and how these effects may interfere with the adaptations to strength and endurance training in women diagnosed with breast cancer have had small sample sizes. Furthermore, no previous study has compared the effects of different training intensities on muscle cells in women with breast cancer during (neo-)adjuvant chemotherapy and it is still uncertain whether high-intensity exercise is feasible in all phases of the treatment. Thus, the aim of this study is to evaluate and compare the effects of high and low-to-moderate intensity exercise on muscle cellular outcomes, muscle function, and cardiorespiratory fitness in women with breast cancer undergoing (neo-)adjuvant chemotherapy. We further aim to investigate if the effects of chemotherapy including taxanes on muscle cells are different from those of taxane-free chemotherapy.

Our hypotheses are as follows.

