## Discussion

The main aim of this study is to compare the effects of a high-intensity strength and endurance training program with those of a low-to-moderate intensity strength and endurance training program on muscle cellular outcomes, muscle function, and cardiorespiratory fitness in women undergoing breast cancer chemotherapy. These results will also be compared with those of the group treated with usual care to investigate how (neo-)adjuvant treatment with chemotherapy will affect these variables and how high and low-to-moderate intensity trainings can counteract the effects of treatment. We hypothesize that the usual care control group will experience negative treatment effects on muscle fiber CSA and mitochondrial function, leading to reduced muscle function and cardiorespiratory fitness. We further expect that both high-intensity training and low-to-moderate intensity training performed by the training groups will counteract the negative treatment effects and that high-intensity training will be superior to low-to-moderate-intensity training. The results of our study are expected to provide insights on how regular exercise during treatment may counteract the side effects of chemotherapy on physical functioning and muscle tissue and how training intensity impacts these effects. Such knowledge can be used to design effective physical exercise programs, helping an increasing number of individuals with breast cancer during and following chemotherapy and possibly reducing the long-lasting side effects and ultimately improve the quality of life.

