Forty women recently diagnosed with breast cancer, with 20 in each group, will give us a larger study population than those in previous studies on muscle cellular outcomes [12,41,42] to draw conclusions from. Furthermore, to our knowledge, this will be the first randomized controlled study comparing the effectiveness between high-intensity strength and endurance training and low-to-moderate intensity strength and endurance training during (neo-)adjuvant treatment on muscle cellular outcomes in patients with breast cancer. We are also recruiting participants who are not willing to undergo muscle biopsies, giving us an even larger study population when analyzing the other outcomes. As high-intensity training is shown to induce larger improvements in maximal oxygen uptake and muscle strength in both healthy individuals and in various patient populations [27,28], it should also be more effective in patients with breast cancer during chemotherapy. However, it is not known to which extent chemotherapy interferes with normal adaptation to physical training, and the high-intensity training is severely more challenging. Consequently, high-intensity training may be less feasible during chemotherapy, and lower adherence to the planned training in some periods of treatment may reduce training effectiveness. However, the feasibility of the current high-intensity training program has been confirmed in the large-scale Phys-Can study [29], in which ~75% of the participants completed the 6-month training program.

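### The 80% and 95% power figures rest on a borrowed effect of about 1.3 SD that is not tied to the main randomised contrast, high versus low-to-moderate intensity

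*Protocol article*

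**What the plan says.** Muscle fibre CSA is the primary outcome (Outcomes). The Sample Size section bases its calculation on a prostate-cancer exercise trial and says that a biopsy study in breast cancer supports similar expectations. It continues: "With a similar effect on muscle fiber CSA", "we need 10 participants in each group to obtain a statistical power of 80% in this study"; and "to further enhance the power up to 95%, we need 16 participants". To allow for dropout, the target is 20 women per training arm who are willing to have biopsies. The section gives no CSA difference, SD, alpha or test, and does not name the comparison to which the effect belongs.

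On the question to be answered, the Discussion says: "The main aim of this study is to compare the effects of a high-intensity strength and endurance training program", set against the low-to-moderate programme. Under Randomization, only these two arms are randomised, 1:1; the usual care group is not. The hypotheses in the Introduction and the opening of the Discussion expect both intensities to counteract the treatment effects, with high intensity superior.

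On earlier evidence, the Introduction says that training in the supporting breast-cancer study "had beneficial effects on muscle fiber CSA and mitochondrial enzymes in the 2 intervention groups". It also says that "no previous study has compared the effects of different training intensities on muscle cells in women with breast cancer" during such chemotherapy.

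**The concern.** A power figure belongs to one contrast. Here it is given for the study as a whole, while the effect behind it comes from another trial in another cancer and is not linked to the contrast that this trial randomises. The supporting breast-cancer evidence, as the article describes it, is a benefit in both training groups. That is not evidence about how far two intensities differ. The article itself says that no such comparison exists for muscle cells in this population.

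If both intensities work, as hypothesised, the gap between them is only part of the effect of high intensity against no training. A design sized on a full training effect would then have less power for the gap than the paragraph suggests. The practical risk lies in interpretation. A non-significant intensity result from a trial described as having 80% to 95% power invites the reading that intensity does not matter, although a moderate difference could easily have been missed.

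**Working it through.** **Inputs from the article.** 10 per group for 80% power; 16 per group for 95%; target of 20 per arm (Sample Size). Two-sided t tests are among the planned analyses (Statistical Analyses). Allocation is 1:1 (Randomization). **Assumed, because not stated:** alpha 0.05 and a two-sample t test. The effect size has to be back-solved.

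**Formula.** With n per group and standardised difference d, power = P(T > t(0.975; 2n − 2)), where T is noncentral t with 2n − 2 degrees of freedom and noncentrality d·√(n/2). The opposite tail is negligible here.

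**Step 1: reproduce the stated figures.**
- n = 10, 80% power: d = 1.325 (noncentrality 1.325 × √5 = 2.963, critical value 2.101).
- n = 16, 95% power: d = 1.318.
- Check: d = 1.325 with n = 16 gives noncentrality 1.325 × √8 = 3.748, critical value 2.042, power 95.2%.

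One effect of about 1.32 SD explains both figures, so they agree with each other.

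**Step 2: sensitivity to the unstated test.**
- Normal approximation: d = 1.25 and 1.27 from the two figures.
- One-sided two-sample t test: d = 1.16 and 1.19.
- Paired within-group t test: 1.00 and 0.97. A paired effect of about 1.0 gives 80% at 10 and 96% at 16.

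The two figures therefore do not identify the test. A paired calculation would not concern a between-group difference at all.

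**Step 3: smallest between-arm difference detectable with 80% power (two-sample, two-sided 5%).**

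| Evaluable per arm | Difference |
|---|---|
| 15 | 1.06 SD |
| 16 | 1.02 SD |
| 20 | 0.91 SD |

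**Step 4: power for the intensity contrast.** The article gives no expected difference, so a range is shown. The value 0.66 is half of 1.32; the half is an assumption.

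| True difference | 10 per arm | 16 per arm | 20 per arm |
|---|---|---|---|
| 1.32 SD | 80% | 95% | 98% |
| 1.0 SD | 56% | 78% | 87% |
| 0.8 SD | 40% | 59% | 69% |
| 0.66 SD | 29% | 44% | 53% |
| 0.5 SD | 18% | 28% | 34% |

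At 0.66 SD, 80% power would need 38 per arm.

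**Step 5: loss, as a sensitivity case only.** Recruiting 20 to keep 16 allows 1 − 16/20 = 20% loss. A 25% loss leaves 20 × 0.75 = 15, with power 93.8% at 1.325 SD and 42% at 0.66 SD.

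**The case against.** The strongest reply is that the documents do not prove a shortfall. They give neither the comparator, effect or SD of the prostate-cancer trial nor the expected difference between intensities. The statement that no study has compared intensities is limited to women with breast cancer, so it does not show what the prostate-cancer trial compared. The 1.3 SD is back-solved, and other tests fit the same two figures. A condensed article may also leave effect size, SD and alpha to the full protocol.

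Most of this stands, and it rules out some stronger readings. A reader might infer that the borrowed effect is training versus no training. That is plausible, but the documents do not say so, and the revised paragraph should not assert it unless the sponsor confirms it. A reader might also infer that the trial lacks 80% power for its main aim. That is a well-supported conditional inference, not an established fact: with 20 evaluable per arm, power stays at 80% or more for any difference of at least 0.91 SD. Nor is there an arithmetic error, since the figures agree with each other. No equivalence claim appears in the article; the misreading of a null result is a risk, not something the authors propose.

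A reader might further set the dropout allowance against the Discussion's report of an earlier study "in which ~75% of the participants completed the 6-month training program". That figure is completion of training in a study of several cancers. Under intention to treat, a woman who stops training can still give a final biopsy, so it does not show that the allowance is wrong. At the implied effect, the consequence would be 93.8% instead of 95%.

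What the reply does not answer is that the article makes an explicit power claim for this study, names a different question as its main aim, and offers no effect for that question. This is more than detail left to another document.

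**Conclusion.** The concern holds as a gap between the power claim and the main contrast. The 80% and 95% figures imply about 1.3 SD on CSA, given a two-sample, two-sided 5% t test, and the article does not connect that effect to high versus low-to-moderate intensity. If it is a full training effect, the intensity difference could reach it only if low-to-moderate training did nothing, which contradicts the article's own hypothesis. The stated power is therefore not shown to apply to the main aim and probably overstates it. The size of the overstatement depends on the true intensity difference, which is unknown. The detectable differences in Step 3 depend on the assumed test and alpha but need no guess about that difference; the 44% to 53% figures also rest on the assumed half effect.

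**What to change.** Revise the sample-size paragraph as follows.

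1. Name the contrast, CSA difference, SD, test and alpha behind the 80% and 95% figures.
2. Unless that difference is justified for high versus low-to-moderate intensity, do not claim 80% or 95% power for that contrast. State instead the difference detectable with 80% power: about 0.9 SD with 20 evaluable per arm, rising to about 1.1 SD with 15. These values assume a two-sample, two-sided 5% test and should be recalculated if the planned test differs.
3. Show 25% loss (15 per arm) as a sensitivity case, not as the expected rate of missing biopsies.
4. State that a non-significant intensity result will be reported with its confidence interval and not read as equivalence.

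The cost is wording and a less favourable power statement. No extra patients or procedures are needed.

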### Randomization

Participants from Haukeland University Hospital will be randomized in a 1:1 ratio into the 2 training groups stratified by treatment (neoadjuvant or adjuvant treatment). The investigator performing the analyses on muscle biopsies will be blinded for this randomization. As described, participation in the usual care group will be from patients living too far away from the study site at Haukeland University Hospital or from Uppsala University Hospital and will not be randomized.

### Intervention

All participants in the training groups will perform both strength and endurance training throughout the course of treatment with chemotherapy, which is approximately 6 months. Trained coaches will guide both strength and endurance training.

#### Strength Training

The first 2-4 weeks after inclusion will be a familiarization period where the participants become familiar with the exercises and tests as well as how to use the Omni scale for self-reported perceived exertion [33] included in the strength training program. During the familiarization period, there will be a test of 10- and 6-repetition maximum (RM) load, which will provide the participants with individualized training loads. The strength training will be performed as previously described [34]. Briefly, the training consists of 2 supervised sessions per week and include the following exercises: seated leg press, chest press, seated leg curl, seated row, leg extension, and standing overhead press by using dumbbells. The low-to-moderate intensity group will perform 12 repetitions for 3 sets at 50% of 6RM load in the first weekly session and 20 repetitions for 3 sets at 50% of 10RM load in the second weekly session (reporting 5-7 on the Omni scale for perceived exertion) [33]. The high-intensity training group will perform 6 repetitions for 3 sets at 6RM load in the first weekly session and 10 repetitions for 3 sets at 10RM load in the second weekly session (reporting 9-10 on the Omni scale for perceived exertion [33].

#### Endurance Training

During the 2-4 weeks familiarization period, participants will familiarize themselves with the use of the heart rate monitor and perceived exertion by using the Borg scale [35] for monitoring the exercise intensity and perceived exertion. All participants will perform the first session with a coach and receive training on how to use the heart rate monitor. Participants in the high-intensity training group will also be given 1-2 extra session with a coach in a gym. Thereafter, the endurance training is home-based and followed up by a coach and will be performed as previously described [34]. Briefly, the low-to-moderate intensity group perform a continuous-based exercise (running, cycling, walking uphill, or any other endurance-based activity) in bouts of at least 10 minutes at an intensity of 40%-50% of the heart rate reserve. The exercise frequency is recommended to be 2-4 times a week with the main aim to reach 150 minutes of moderate intensity per week. The high-intensity group performs high-intensity interval exercise. The sessions will consist of 2-minute intervals (running, cycling, walking uphill, or any other endurance-based activity) at an intensity of 80%-90% of the heart rate reserve (at the end of the third session) with 2 minutes of rest between intervals. During the first week, after familiarization, each session will consist of 6 intervals. Thereafter, 1 bout will be added every fourth week until 10 bouts per session are reached as the maximum, corresponding to 75 minutes of high-intensity training per week.

### Procedures

#### Muscle Biopsy Sampling

Muscle biopsies are obtained from the midsection of the vastus lateralis muscle under local anesthesia (xylocaine adrenaline, 10 mg·ml^-1^ + 5 μg·ml^-1^, AstraZeneca). Briefly, a 1-2-cm incision will be made in the skin and the fascia of the vastus lateralis muscle. Biopsies are collected using a 6-mm Pelomi needle (Bergström technique) with manual suction to obtain muscle samples (~200 mg). Biopsies will be rinsed in ice cold saline (0.9% NaCl) and carefully dissected free of visual fat, connective tissue, and blood. All pieces but 2 will be frozen in isopentane, precooled on dry ice, and stored at –80 °C for later analysis. The last 2 pieces (~10 mg) will be transferred to 500 μL of RNAlater stabilization solution (Invitrogen) and stored at 4 °C for at least 24 hours before 1 piece is transferred to –20 °C for long-time storage while the RNAlater solution is removed from the last piece before long-term storage at –80 °C.

#### Muscle Analyses

##### Muscle Fiber Size

Muscle fiber CSA represents the primary muscle cellular outcome. Muscle fiber CSA will be measured by immunohistochemical analysis of the cross-sections of the muscle biopsies. Briefly, transverse serial sections of the muscle biopsy (8-μm thick) will be cut using a cryostat microtome at –22 °C and mounted on glass slides. Serial cross-sections will be immunohistochemically stained for fiber types (type I, type IIa, and IIx) for CSA measurements. Muscle fiber CSA will be measured for the different fiber types separately.

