### Study Design

This study is a 2-group randomized controlled trial (Figure 1). The participants will be randomly allocated into 1 of the 2 training groups: one group performing the combination of strength and endurance training with high intensity and the other group performing the training with low-to-moderate intensity during (neo-)adjuvant treatment for breast cancer. To measure the effect of the treatment itself, a parallel usual care group receiving no supervised training will be recruited from another pool of patients. This will be from patients living too far away from the study site to participate in training and from a usual care control group from another substudy within the Phys-Can consortium carried out at Uppsala University Hospital [31]. The usual care group will have the same inclusion and exclusion (see below) criteria as the 2 training groups in this study. Muscle biopsies, questionnaires, and blood samples will be collected from the training groups before the first chemotherapy cure (T0). The first 2-4 weeks after cure 1 will be used as a familiarization period for tests and exercises and for completing the remaining T0 tests. Testing will include measurements of physical capacity, body composition, and physical activity levels. All measurements, including muscle biopsies, questionnaires, and blood samples, will be repeated halfway into the treatment (T1) and after completion of treatment (T2). In the participants in the usual care group, measurements will be performed at T0 and T2 only. Training will start between cure 2 and cure 3 and will last throughout the treatment period, which is approximately 6 months.

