### Outcomes

The primary outcome for this study is muscle fiber CSA, whereas secondary outcomes include muscle function, cardiorespiratory fitness, regulators of muscle fiber size and function (including mitochondrial enzymes, heat shock proteins, protein control systems, and DNA damage), and myokines with putative antitumor effects. All outcomes are listed in Table 1.

**Table 1 table1:** Outcomes and assessments.

Outcomes and specific variables			Assessment
Muscle fiber size (muscle fiber cross-sectional area)			Cross-sections of muscle biopsies
Number of myonuclei per muscle fiber (myonuclei/fiber)			Cross-sections of muscle biopsies
Number of satellite cells per muscle fiber (satellite cell/fiber)			Cross-sections of muscle biopsies
Proteins involved in muscle hypertrophy (PI3K^a^/Akt^b^/mTOR^c^-pathway, including but not limited to mTOR^c^, P70s6k^d^, 4EBP1^e^, eIF4A^f^)			Western blot
Proteins involved in muscle protein degradation (including but not limited to FOXO^g^, ubiquitin ligase E2, LC3^h^ (I and II), p62^i^, myostatin, as well as ubiquitinated proteins)			Western blot

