##### Myokines With Potential Antitumor Effects

Exploratory analyses on the effects of the training on the expression levels of myokines, previously proposed to have an antitumor effect, will be conducted. Relevant targets, including, but not limited to, interleukin (IL)-6, IL-15, secreted protein acidic and rich in cysteine, and TNF-related weak inducer of apoptosis will be evaluated at the mRNA level by real-time polymerase chain reaction analyses (RNA extracted from biopsies) and at the protein level by western blot and enzyme-linked immunosorbent assays (muscle and blood samples). Blood samples will be obtained by venipuncture and participants are asked to avoid smoking and alcohol and not to engage in any strenuous physical activity 24 hours before the blood sample collection. The levels of IL-6, IL-8, IL-10, IL-1β, IFN-γ, tumor necrosis factor (TNF)-α, and TNFR1 will be measured using enzyme-linked immunosorbent assay–based methods. Frozen sera will be saved for further analyses that can be included later.

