### Statistical Analyses

Data will be analyzed according to the intention-to-treat principle. Analyses will include standard descriptive statistics, 2-sided *t* tests, correlation, regression, and 2-way repeated-measures analysis of variance or the comparable nonparametric test as necessary to examine the differences between and within groups at T0, T1, and T2. In addition, a per-protocol analysis, that is, adherence to the protocol, will be conducted. Should imbalances in important variables be detected, sensitivity analyses will also be added including these as covariates in the model.

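### Muscle fibre CSA is the single primary outcome, but it is measured in three fibre types and at two follow-up times, and the protocol article does not say which measure or time point is primary

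*Protocol article*

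**What the plan says.** The Outcomes section is plain: "The primary outcome for this study is muscle fiber CSA". The Discussion repeats this. Muscle Fiber Size, under Muscle Analyses, calls CSA the primary muscle cellular outcome and then divides it: "Serial cross-sections will be immunohistochemically stained for fiber types (type I, type IIa, and IIx) for CSA measurements", followed by "Muscle fiber CSA will be measured for the different fiber types separately". No pooled, weighted or lead fibre measure is named.

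Under Study Design, the training groups have biopsies at T0, T1 and T2. For usual care, "In the participants in the usual care group, measurements will be performed at T0 and T2 only". No section says whether T1 or T2 is the primary time point.

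Statistical Analyses lists two-sided t tests, correlation, regression and two-way repeated-measures ANOVA or a nonparametric counterpart, "to examine the differences between and within groups at T0, T1, and T2". No alpha is given.

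Sample Size treats CSA as one outcome with one effect: 10 per group for 80% power, 16 for 95%, with 20 per training group to be recruited for biopsy to allow for dropout. The effect size, the SD and the fibre type behind these figures are not given.

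On a separate matter, Outcomes lists myokines among the secondary outcomes, while the myokine section announces "Exploratory analyses on the effects of the training on the expression levels of myokines".

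**The concern.** A primary outcome should identify the one result that decides the trial's main question. Here one label covers three measurements at two follow-up times. Suppose type II fibres differ between the arms at T2 and type I fibres do not, or a difference appears at T1 and is gone by T2. The article does not say which result answers the primary question. The choice could then be made after the results are seen, and the chance of at least one false-positive CSA finding would exceed the per-test level.

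The sample size is also affected. If all three fibre types are meant to be primary and the error rate is controlled across them, the power for each type is lower than the figures stated.

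**Working it through.** **Inputs from the article.** Three fibre types; two follow-up times in the training groups; two-sided tests; 10 per group for 80% power and 16 for 95%; 20 per training group recruited for biopsy; 1:1 randomisation.

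**Assumptions.** Two-sided alpha of 5% per test. Correlations between fibre types, and between T1 and T2, are not in the article, so a range is shown.

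**1. The stated sample size.** Without an effect size, SD or alpha, it cannot be reproduced from stated inputs. What can be checked is whether 10 and 16 fit one test. For a two-sample t test with n per group, power is P(|t′| > t(1−α/2; 2n−2)), where t′ is noncentral t with 2n−2 degrees of freedom and noncentrality d√(n/2).
- n = 10, α = 0.05, power 80%: d = 1.325 (noncentrality 1.325 × √5 = 2.96).
- n = 16 at the same d: noncentrality 1.325 × √8 = 3.75, power 95.2%, and 16 is the smallest n that reaches 95%.

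So 10 and 16 are consistent with one two-sided 5% test. The fit is not unique: the normal approximation gives d = 1.253 and n = 17, and a one-sided t test also gives 17.

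**2. False-positive rate, high versus low-to-moderate at T2, three fibre types, unadjusted.** If independent: 1 − 0.95³ = 0.143. With correlation, by simulation (t tests on change scores, 16 per group, 40,000 runs):

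| Correlation between fibre types | At least one p < 0.05 |
|---|---|
| 0 | 14.2% |
| 0.3 | 13.4% |
| 0.5 | 12.8% |
| 0.7 | 11.1% |
| 0.8 | 10.0% |
| 0.9 | 8.4% |

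**3. Same contrast, T1 tested separately as well (six tests).** If independent: 1 − 0.95⁶ = 0.265. In simulation: 23.6% with correlations of 0.3 between fibre types and 0.5 between times, falling to 11.6% with both at 0.9.

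**4. Power if the three types are co-primary, at d = 1.325.** Bonferroni alpha is 0.05/3 = 0.0167.
- 16 per arm: 87.9%, against 95.2% for one test.
- 20 per arm (noncentrality 1.325 × √10 = 4.19): 94.9%, against 98.3% for one test.
- 80% power needs 14 per arm in place of 10.

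Holm is never less powerful than Bonferroni, so these are lower bounds for Holm at this d.

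**The case against.** The strongest reply is that this is a condensed article and that the alpha, the time point and any multiplicity rule may stand in a full protocol or analysis plan that is not shown. That is fair for alpha and the correction method, and their absence is not the point here. The definition of the primary outcome is different: the article takes it up and leaves one name on three measurements.

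The sentence on separate measurement describes laboratory work, and measured separately does not strictly mean tested separately. That stands, so the error rates above are conditional on unadjusted testing. A group-by-time ANOVA could also combine T1 and T2 in one test, although it would not combine the fibre types.

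Three stronger readings are tempting, and the article does not support them.
- **That p < 0.05 in any fibre type, at either time, between or within groups, counts as primary success.** No such rule is written. The article only fails to exclude it.
- **That the deciding group comparison is open.** Study Design describes a two-group randomised trial, Randomization says usual care is not randomised, and the Discussion gives high versus low-to-moderate as the main aim. The hypotheses do include comparisons with usual care, but nothing makes them co-primary.
- **That the error rate could reach 46%.** Usual care has no T1 biopsy, so there are 3 × (1 pair at T1 + 3 pairs at T2) = 12 between-group tests, and 1 − 0.95¹² = 0.46. The pairs share groups, so these tests cannot be independent. Simulation gives 42.2% with uncorrelated outcomes and 22.1% to 38.8% with correlated ones, and even those figures count comparisons the article does not call primary.

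The loss of power is also modest: 88% with 16 per arm is still above the 80% benchmark.

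**Conclusion.** The point holds in a limited form. The primary outcome is badly fixed: one named outcome, three separate fibre-type measures, two follow-up times, and no statement of which is primary, beside a sample size that fits a single test.

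On the randomised contrast at T2, unadjusted testing of all three types would give a false-positive rate of about 8% to 14%, and more if T1 is tested separately. This rests on an assumed two-sided 5% level, on assumed correlations from 0.9 down to 0, and on the three types being tested without adjustment. The power figures rest on d of about 1.32, which is back-calculated and not stated in the article.

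The conflicting status of the myokines is real, but it is minor and has no bearing on the primary error rate.

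**What to change.** Before the training-group data are analysed, record one primary analysis: the randomised high minus low-to-moderate difference in one CSA measure at T2, adjusted for T0 CSA. The sponsor should choose the measure; a pooled or fibre-type-weighted CSA would be examples. Alternatively, keep the three fibre types co-primary with a Holm correction and restate the power.

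Classify the remaining fibre types, T1, the within-group tests and the non-randomised usual-care comparisons as secondary or descriptive. State the alpha.

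Separately, give the myokines one status in both Outcomes and the myokine section.

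The cost is a change of wording, with no new patients or procedures, since T0 CSA is already collected. The downside is less freedom to headline another fibre type. Timing matters: the Results section puts the start of the Haukeland analyses in fall 2022 and says the Uppsala analyses were already under way. If training-group CSA data have been examined by the time the choice is recorded, the record should say so.
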